### Quality control

2.15

This study will introduce and promote an ISO quality management system. Personnel at all levels will receive the necessary training in management and quality awareness. A quality control system will be established during project implementation, and relevant quality control measures and evaluation plans will be formulated. The project lead unit will assign special personnel to conduct quality control and supervision of this study, including clinical data collection standards and data verification quality control measures. In addition, the project involves task verification and quality control of participating units to ensure completion. A quality-verification document was created and stored for archival purposes. In addition, Guang’anmen Hospital of the China Academy of Chinese Medical Sciences selected a third party to establish the clinical database of the participants and conducted a statistical analysis of the data.

### Statistical analysis and method

2.16

SAS 9.4 statistical software will be used, and full analysis set (FAS) and protocol compliance set (PPS) analyses will be performed on the efficacy indicators. A safety dataset analysis should be conducted for adverse reactions. All statistical tests will be conducted bilaterally, and statistical significance will be set at *p* ≤ 0.05. We will analyze whether there are outliers in the data and conduct a professional analysis of outliers to decide whether to accept or reject them. After this, we will analyze the data for missing values and conduct a professional analysis to determine whether the missing values are listed as missing or data transferred. The proportion of shedding cases should not exceed 10%; otherwise, analysis and explanation should be provided. The measurement data were described as mean, standard deviation, median, minimum, and maximum whereas counting data were described as frequency, percentage, etc. Quantitative data analysis will be performed using *t*-tests, rank-sum tests, etc. Counting data analysis will be performed using chi-square tests, ridit analyses, etc. Survival data analysis will be performed using the Kaplan–Meier method, Wilcoxon rank sum test, or log-rank test. A Cox-proportional risk regression model was used for multivariate survival analysis.

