### Intervention

2.8

The intervention group will receive YWJP, whereas the control group will receive YWJP placebo. Patients will take one pack each time, dilute it with boiling water, and administer it twice daily (in the morning and evening). The course of treatment will be 4 weeks, and six courses are planned.

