### Outcome measurements

2.12

The 2-year DFS rate as the primary outcome and DFS, OS, 1- to 3-year cumulative recurrence and metastasis rate, and 1- to 3-year cumulative survival rate as the secondary outcome will be calculated at the end of follow-up. The lymphocyte count-to-monocyte count ratio (LMR) (59), lymphocyte count-to-neutrophil count ratio (LNR) (60), prognostic nutritional index (PNI) (61), Quality of Life Questionnaire of Stomach 22 (QLQ-STO22) (62), M. D. Anderson Symptom Assessment Scale Gastrointestinal Tumor Specific Module (MDASI-GI) (63), Postgastrectomy Syndrome Assessment Scale-45 (PGSAS-45) (64) (diagnosis of the syndrome should refer to the 2014 *Guidelines of Diagnosis and Therapy in Oncology with Traditional Chinese Medicine*), and other secondary outcome indicators will be collected at weeks 0–6, whereas the total fat area (TFA) (65), visceral fat area (VFA) (66), subcutaneous fat area (SFA) (67), visceral adiposity index (VAI) (68), and tumor markers will be collected at weeks 0, 3, and 6. All measurement results will be recorded in the case report form (CRF). The details of outcome measurement projects are shown in **Table 1**.

**Table 1 T1:** Treatment stage flowchart.

Item		Baseline	Treatment observation				Follow-up
Number of visits		1st time	2nd time	3rd time	4th time	*N*th time	*N* + *X*th time
Observation time		Days −7 to 0	Days 28–35	Days 56–63	Days 84–91	End of *N*th treatment course	Once every 3 months
Inclusion/Exclusion criteria		√					
Sign informed consent form		√					
Collect medical history							
Demographic data		√					
Diagnosis and TNM classification		√					
Past history and comorbidities		√					
Clinical observation							
Vital signs		√	√	√	√	√	√
Physical examination		√	√	√	√	√	√
Survival situation		√	√	√	√	√	√
MDASI-GI		√	√	√	√	√	√
Tongue and pulse condition		√	√	√	√	√	√
TCM syndrome		√	√	√	√	√	√
Imaging examination	PET-CT/CT/X-ray	√			√	√	√
	MRI, B-mode ultrasonography	*	*	*	*	*	*
	Bone scanning	*	*	*	*	*	*
	Gastroscope	*	*	*	*	*	*
Tumor marker		√	*	*	√	*	*
Indicators related to fat distribution		√	*	*	√	*	*
QLQ-STO22		√	√	√	√	√	√
PGSAS-45		√	√	√	√	√	√
Safety observation							
Blood routine		√	√	√	√	√	√
Hepatic and renal function		√	√	√	√	√	√
Urine and stool routine		*	*	*	*	*	*
Electrocardiogram		√	√	√	√	√	√
NCI adverse reaction			√	√	√	√	√
Adverse event			√	√	√	√	√
Other work							
Efficacy evaluation			√	√	√	√	√
Drug combination			√	√	√	√	√

*This check is optional.

√ This check is necessary.

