### Data collection and management

2.14

Patients will undergo periodic follow-up (once a month during the treatment period and once every 3 months during the follow-up period, including electronic questionnaires or telephone follow-up). After surgery, they will be observed for at least 3 years. Data on vital signs, physical examination, weight, height, body surface area, BMI, ECOG score, KPS score, QLQ-STO22, MDASI-GI, PGSAS-45, peripheral blood inflammatory indicators, blood and urine routine, complete biochemical tests, electrocardiogram, and blood tumor markers will be collected for each treatment cycle and during follow-up visits every 3 months. For participants who did not experience disease progression after completing six courses of treatment, imaging follow-up was conducted every 3 months for 2 years post-surgery and then every 6 months after that until disease recurrence or initiation of alternative therapies. The basic information of the patients and the relevant information required for the study will be recorded in the CRF. Only authorized researchers, representatives of research-undertaking units, ethics committees, and higher-level management departments can access patient records upon reasonable request. No public reports of the results of this study disclose the patient’s name or identity. The research team will protect the privacy of the patient’s medical data as much as possible within the scope permitted by law.

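### Outliers and missing values are settled by undefined judgement, and repeatedly measured secondary outcomes get two-group tests with no stated use of baseline

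*Protocol article*

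**What the plan says.** Section 2.16 (Statistical analysis and method) sets three rules that bear on the quantitative outcomes.

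- Outliers: the team will "conduct a professional analysis of outliers to decide whether to accept or reject them".
- Missing values: as the next step, it will "conduct a professional analysis to determine whether the missing values are listed as missing or data transferred".
- Tests: "Quantitative data analysis will be performed using *t*-tests, rank-sum tests, etc". The only regression model named is a Cox model, for survival data.

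The outcomes concerned are measured at baseline and repeatedly. Section 2.12 says that LMR, LNR, PNI, QLQ-STO22, MDASI-GI, PGSAS-45 and "other secondary outcome indicators will be collected at weeks 0–6", and that the fat indices and "tumor markers will be collected at weeks 0, 3, and 6". Section 2.14 says that the questionnaires, peripheral blood inflammatory indicators and blood tumor markers, among others, "will be collected for each treatment cycle and during follow-up visits every 3 months". On treatment length, Section 2.8 states: "The course of treatment will be 4 weeks, and six courses are planned".

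**The concern.** The outlier rule is a positive permission to delete data on inspection. In a trial of recurrence, a very high CEA, CA724 or CA199, an abnormal blood ratio or a poor symptom score may be the signal itself. If such values are rejected, the arm with more recurrences loses more of its bad values and looks better than it is. The missing-value rule comes next in sequence, so a rejected value could become a missing one and then be replaced by a method that is not defined.

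The second matter is efficiency. A plain two-group comparison of final values makes no use of baseline measurements that the trial pays to collect. A change score uses them, but less efficiently than adjustment does.

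**Working it through.** **Plan's own figure.** The article gives no standard deviation, correlation or effect size for these outcomes. The only sample-size figure is for the primary outcome: 96 per arm before dropout, from 43.9% v 63.9%, two-sided 0.05, power 0.80 (Section 2.11). The two-proportion formula gives 97 per arm with pooled variance and 94 unpooled. So 96 is reproduced to within two patients and is used below as the arm size.

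**Step 1: what the outlier rule leaves open.** Section 2.16 gives no numeric criterion, no restriction to verified data errors, no timing relative to unblinding, and no analysis with all values kept. It applies to the data in general, so it covers the markers, ratios and scores listed in Section 2.12.2.

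**Step 2: what rejection could do.** This is an illustrative simulation; every input except the arm size is assumed. It has 96 per arm and a log-normal marker (log mean 1, log SD 0.6). Recurrence by the visit is 20% v 12%, with recurring patients shifted upward on the log scale. Values above the pooled Q3 + 3 × IQR are rejected. There were 3,000 simulated trials per row.

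| Log shift | Values rejected (of 192) | Share from recurring patients | Mean difference, all values | After rejection | Fraction left |
|---|---|---|---|---|---|
| 1.0 | 5.1 | 90% | 0.44 | 0.27 | 0.27/0.44 = 61% |
| 1.5 | 10.5 | 97% | 0.88 | 0.38 | 0.38/0.88 = 43% |
| 2.0 | 18.8 | 99% | 1.67 | 0.35 | 0.35/1.67 = 21% |

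**Step 3: what baseline adjustment gains.** Let ρ be the baseline-outcome correlation (not given; 0.5 to 0.7 assumed). Relative to a t-test on the final value (variance 1), a change score has variance 2(1 − ρ) and ANCOVA has 1 − ρ². The ratio of ANCOVA to change score is (1 − ρ²)/[2(1 − ρ)] = (1 + ρ)/2.

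| ρ | 1 − ρ² | Cut v final value | (1 + ρ)/2 | Cut v change score |
|---|---|---|---|---|
| 0.5 | 0.75 | 25% | 0.75 | 25% |
| 0.6 | 0.64 | 36% | 0.80 | 20% |
| 0.7 | 0.51 | 49% | 0.85 | 15% |

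With 96 per arm the detectable standardized difference is (1.960 + 0.842) × √(2/96) = 0.40. At 0.4, a final-value t-test has 79.1% power. ANCOVA has 89.3%, 93.4% and 97.3% at ρ = 0.5, 0.6 and 0.7, and a change-score test has 79.1%, 87.3% and 94.7%. For 80% power, a final-value test needs 99 per arm and ANCOVA needs 74, 63 and 51. At ρ = 0.3 the gain is small: the variance cut is 9% and power is 82.8%.

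**Step 4: which visit could carry the comparison.**

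- Section 2.12 text: markers and fat indices at weeks 0, 3 and 6.
- Table 1: both are required only at baseline and days 84–91, and optional at every other visit, including the end of later courses and follow-up.
- Section 2.14: tumor markers every treatment cycle and every 3 months in follow-up.

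Taken literally, weeks 3 and 6 are days 21 and 42. Neither falls in a Table 1 visit window (days 28–35, 56–63, 84–91). If the unit is meant to be four-week courses, the third ends on day 3 × 28 = 84, which matches Table 1, but the sixth is then optional there. The three places cannot all hold.

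**The case against.** The strongest reply is that much of this belongs in a statistical analysis plan that is not shown. A condensed article need not name a longitudinal model, its covariates, a contrast or a scale, so their absence alone is no error. That stands. The model is therefore offered as an improvement on the methods the article does name. The outlier and missing-value rules are different, because they are stated.

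Several stronger readings are tempting, and the text does not support them:

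- *Baseline values are discarded.* The list of tests is open-ended and does not say what the tests are applied to. A t-test on change from baseline would use baseline.
- *Each visit gets its own 5% test.* This is not stated. Under independence, 3 or 6 such tests would give 1 − 0.95³ = 14.3% or 1 − 0.95⁶ = 26.5%. That is an upper guide to a plan nobody has written down.
- *Recurring patients are removed.* The rule concerns values. Rejecting a CEA result does not remove a recurrence from the DFS count.
- *Missing values will be carried forward.* The wording is unclear, and carry-forward is only one guess at its meaning.

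The article also describes double-blinding with statisticians outside the trial (Section 2.7) and third-party data handling and analysis (Section 2.15). These make blinded review of outliers possible, but no sentence says it will happen. Finally, rank-sum tests tolerate skewed markers, which lessens any need to reject values but does not withdraw the permission to do so.

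**Conclusion.** The point holds as a moderate one about secondary outcomes. The firmer part is the discretion over outliers and missing values: it is written into the plan, it is not tied to verified errors or to the time before unblinding, and it can act on the values that recurrence is expected to produce. The size of any distortion cannot be known from the document. The simulation shows only that it could be large under the assumed recurrence rates, shifts and rejection rule.

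The second part concerns precision. An unadjusted comparison is valid under randomization, so the variance cuts are not a correction of bias, and they rest on an assumed correlation of 0.5 to 0.7. Neither part changes the primary 2-year DFS rate or the sample size.

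**What to change.** 1. Keep every value confirmed against source. Delete only verified errors, with the decision documented before unblinding.
2. Remove the filling option for missing values, or define what it means and when it applies.
3. Replace the two-group tests for these outcomes with a baseline-adjusted analysis. Use a mixed model for repeated measures (arm, visit, arm-by-visit, baseline value), or ANCOVA where there is one post-baseline value. Analyse markers and cell ratios on the log scale, which tempers extreme values without deleting them.
4. Name the contrast visit for each outcome. For markers and fat indices it should be a visit where measurement is required, so Section 2.12, Table 1 and Section 2.14 must first be reconciled.
5. Add a sensitivity analysis for missing data. The mixed model relies on missing-at-random. That is open to doubt here, since Section 2.6 lists death, poor compliance and loss to follow-up as grounds for withdrawal and the Discussion expects substantial dropout.

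The cost is a few sentences of wording and slight additional programming in SAS 9.4, which is already named. The main downside is the reliance on missing-at-random, which item 5 addresses.

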### Inclusion criteria

2.4

1. Research cases must be sourced from real-world registration platforms.2. Stage II–III non-esophageal gastric junction GC that meets the diagnostic criteria and does not indicate tumor recurrence or metastasis by imaging.3. Patients with GC who underwent radical gastrectomy (R0) within 8 months after surgery and completed at least six cycles of adjuvant chemotherapy with standard regimens (XELOX and SOX).4. Eastern Cooperative Oncology Group (ECOG) performance status score of 0–2.5. Patient ages ranging from 18 to 75 years, with no sex limitations.6. Expected survival time ≥3 months.7. Patients who voluntarily participated in the study, signed an informed consent form, and participated in the follow-up.

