### Randomization and blinding

2.7

This study will apply an Interactive Web Response System for central randomization and implement hidden allocation schemes. Patients will be randomly divided into intervention and control groups in a 1:1 ratio based on central randomization. The R software (V3.3.3) will be used to generate random sequences with three rounds of cyclic random statements. The blinding level will be double-blind, in which neither the researcher nor the participant have any idea of the specific details of the study. Anonymizing will be performed by statisticians who did not participate in the clinical trials and divided into two levels. This trial will establish a dedicated “emergency letter” for clinical trials that can only be urgently unblinded when the patient experiences an emergency. Handling this situation requires a clear understanding of the patient’s medication information.

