### Sample size

2.11

This was a randomized controlled trial. The primary outcome was the 2-year disease-free survival (DFS) rate of patients with GC after surgery. It was estimated that the DFS rate 2 years after surgery in the control group was 43.9%, whereas the DFS rate in the intervention group was 63.9%. For α = 0.05 (bilateral), β = 0.2. Assuming that the enrollment rate of the study patients remained unchanged, the proportion of the intervention group to the control group was 1:1. The sample size for N1 was 96 cases in the intervention group, and for N2 was 96 cases in the control group, as calculated using the PASS 11 software. However, a detachment rate of 10% must be considered in the research process. Therefore, the intervention and control groups comprised 106 patients each (212 patients total).

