#### Primary outcome

2.12.1

The primary outcome of this study is the 2-year DFS rate after surgery, which refers to the proportion of patients who have not experienced recurrence, metastasis, or (for any reason) death within 2 years after surgery.

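### Free improvement: prespecify stage (II vs III) in the primary 2-year DFS comparison, because the tests listed for proportions do not use it

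*Protocol article*

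**What the plan says.** - Inclusion criteria (2.4) pool two stages: "Stage II–III non-esophageal gastric junction GC that meets the diagnostic criteria".
- Table 1 makes the TNM classification a required baseline item, so stage is known for every patient at entry.
- Randomization and blinding (2.7): "Patients will be randomly divided into intervention and control groups in a 1:1 ratio based on central randomization". No stratification factor is mentioned.
- Primary outcome (2.12.1) is binary: "the proportion of patients who have not experienced recurrence, metastasis, or (for any reason) death within 2 years after surgery".
- Statistical analysis and method (2.16) lists methods by type of data. Count data get chi-square and ridit. Survival data get Kaplan–Meier with a Wilcoxon or log-rank test. The only adjusted method is the last sentence: "A Cox-proportional risk regression model was used for multivariate survival analysis". It names no covariates, and no test in the section is assigned to the primary outcome.

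**The concern.** Stage is an obvious candidate prognostic factor within the eligible population, and it is already collected. If it predicts 2-year DFS, a comparison that ignores it leaves explainable variation in the noise. A chance difference in stage mix between arms would also pass straight into the estimated treatment difference. The Discussion relies on 1:1 allocation to balance the arms, but with about 100 patients per arm and no stratification described, balance on stage is not assured. If stage is brought in only after an imbalance has been seen, the adjusted result can be challenged as post hoc. What is at stake is precision and the credibility of any later adjustment, not the validity of the test.

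**Working it through.** **Inputs from the article (2.11).** 2-year DFS 43.9% (control) and 63.9% (intervention); "For α = 0.05 (bilateral), β = 0.2"; 1:1 allocation; 96 per arm, raised to 106 per arm for 10% dropout.

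**Inputs assumed.** The article gives no stage mix and no stage-specific DFS. The ranges used are a stage III share s of 50%, 60% or 70%, and a stage II minus stage III gap g in control 2-year DFS of 10, 20, 30 or 40 points. The treatment odds ratio is the same in both stages.

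**Step 1: reproduce the sample size.** For an unadjusted two-proportion test,

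n per arm = [1.960·√(2·p̄·q̄) + 0.8416·√(p₁q₁ + p₂q₂)]² / d²

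with p̄ = (0.439 + 0.639)/2 = 0.539 and d = 0.200.

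- 2·0.539·0.461 = 0.4970, square root 0.7050
- 0.439·0.561 + 0.639·0.361 = 0.4770, square root 0.6906
- n = (1.3818 + 0.5812)² / 0.04 = 96.3, so 97

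This agrees with the stated 96 to within one patient. Power is 79.9% at 96 per arm and 83.7% if all 106 per arm are analysed. For dropout, 96 × 1.1 = 105.6, which gives the stated 106. The planned 80% therefore already belongs to an unadjusted test.

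**Step 2: build stage-specific rates that keep the planned overall rates.** Control stage III rate = 0.439 − (1 − s)·g; control stage II rate = that + g. Example with s = 0.60 and g = 0.30: stage III 0.319, stage II 0.619. The common odds ratio that returns 63.9% overall gives treated rates of 0.533 and 0.798 (check: 0.6·0.533 + 0.4·0.798 = 0.639).

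**Step 3: compare the tests.** 200,000 simulated trials per scenario, 96 per arm, simple 1:1 randomisation, two-sided 5%. Each cell shows power of the unadjusted chi-square → stage-stratified CMH.

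| Gap g | s = 50% | s = 60% | s = 70% |
|---|---|---|---|
| 10 points | 80.0 → 80.1 | 79.9 → 79.9 | 80.1 → 80.1 |
| 20 points | 80.1 → 81.3 | 80.3 → 81.3 | 80.0 → 80.9 |
| 30 points | 80.1 → 83.3 | 80.2 → 83.0 | 80.2 → 82.6 |
| 40 points | 80.0 → 86.0 | 79.9 → 85.2 | 80.1 → 84.4 |

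The gain is about 0, 1, 3 and 4 to 6 points. With no treatment effect, both tests reject in 4.9% to 5.1% of trials.

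**Step 4: chance imbalance.** The SD of the between-arm difference in stage III share is √(2·s·(1 − s)/96), which is 7.2, 7.1 and 6.6 points for s = 50%, 60% and 70%. The simulated probability of a difference of 10 points or more is 17%, 16% and 13%. A 10-point imbalance shifts the unadjusted difference by about 0.10 × g, that is 1 to 4 points. The standard error of the difference is √(0.4770/96) = 7.0 points, so the shift is about 0.14 to 0.57 of a standard error.

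**The case against.** The strongest reply is that this is a condensed article. Covariates, stratified tests and the strata of a central randomisation system are commonly left to the full protocol or the analysis plan, and neither is shown. Section 2.16 is an open-ended list by data type. A reader might infer that the plan declares an unadjusted primary comparison. It does not: no test is assigned to the primary outcome, and the Cox model could well include stage. That objection stands, and it is why the point is an improvement and not an error. What remains is narrower: nothing listed for a proportion uses stage, and a Cox model analyses time to event, not the 2-year proportion on which the trial is sized.

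A second reply concerns size. Much larger gains can be produced by simulating a log-rank test with a within-stage hazard ratio of 0.60, 60% stage III, 106 per arm and 29 months of follow-up. Power then rises with stratification from 81% to 85%, 76% to 85% and 70% to 84% for stage hazard ratios of 2, 3 and 4. Those figures do not describe this trial's primary comparison. The declared outcome is a proportion, and a within-stage hazard ratio of 0.60 implies treated 2-year DFS of only 60.5%, 59.8% and 59.2%, not the planned 63.9%. Much of the apparent shortfall comes from that smaller effect. Stage hazard ratios of 3 and 4 also imply control stage gaps of 37 and 45 points.

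**Conclusion.** This is a free improvement. At the article's own rates and 96 per arm, a stage-stratified primary test would add about 0 to 6 points of power: about 1 point for a 20-point stage gap and about 3 points for a 30-point gap. It would also remove a shift of roughly 1 to 4 points in the 13–17% of trials with a stage imbalance of 10 points or more. These figures rest on the assumed stage mix, stage gap and common odds ratio, and on simple randomisation; if the full protocol stratifies randomisation by stage, the imbalance part largely falls away.

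Two stronger readings are not supported. A reader might infer that the trial is underpowered because stage is ignored; the planned 80% is met without adjustment, and power is lower only relative to an adjusted analysis. A reader might also infer that a stage imbalance would make the unadjusted test invalid; its type I error stays near 5%, and the possible shift is small against the 20-point target, though it could matter for a result near the significance threshold.

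**What to change.** Before unblinding, state that the primary analysis of the 2-year DFS rate is a Cochran-Mantel-Haenszel test with a stratified risk difference and 95% CI, stratified by pathological stage (II vs III). Report the unadjusted chi-square as a sensitivity analysis. Use the stage-stratified log-rank test and Cox model for the secondary DFS time and OS. They should not replace the primary comparison: that would swap the 2-year proportion counted from surgery for a time-to-event outcome counted from randomisation (2.12.2), and it would no longer match the calculation in 2.11.

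The cost is a few sentences. No new data are needed, because TNM is already required at baseline, and the sample size stands. In the scenario with the weakest stage effect examined (a 10-point gap), stratification cost no power. If the full protocol or the analysis plan already specifies this, the sponsor need only confirm it.
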